## Section 1: Administrative information

### 1a. Trial title

A multicentre, randomised trial of stabilisation with nasal high flow during neonatal endotracheal intubation: The SHINE Trial

### 1b. Trial registration

ANZCTR registration number ACTRN126128001498280

https://www.anzctr.org.au/Trial/Registration/TrialReview.aspx?id=375880&isReview=true

### 2. SAP version

Version 1 (dated 11 January 2021)

Version 2 (dated 18 June 2021)

### 3. Protocol version

This document is based on information contained in the study protocol of the SHINE Trial version 6 (dated 13 October 2020).

### 4. SAP revisions

The manuscript was initially submitted to Trials on April 1, 2021, prior to completion of primary data collection. Version 2 (dated 18 June 2021) made amendments following reviewer comments. These amendments were made prior to any data analysis occurring.

## Section 2: Introduction

### 7. Background and rationale for trial

Endotracheal intubation is an essential but potentially destabilising procedure for neonates. With an increased focus on avoiding mechanical ventilation, particularly in preterm infants, there are fewer opportunities for clinicians to gain proficiency in this important emergency skill. Rates of successful intubation at the first attempt are relatively low, and adverse event rates including desaturation and bradycardia are high, when compared with intubations in paediatric and adult populations. Interventions to improve operator success and patient stability during neonatal endotracheal intubation are needed. Using nasal high flow therapy during apnoea extends the safe apnoeica time of adults undergoing upper airway surgery and during endotracheal intubation [1]. This technique is untested in neonates.

The SHINE (Stabilisation with nasal High flow during Intubation of NEonates) trial is a multicentre, randomised controlled trial comparing the use of nasal high flow (nHF) during neonatal intubation with standard care (no nHF). Intubations are randomised individually and stratified by site, use of premedications, and postmenstrual age of the infant (≤ 28 weeks’ gestation; > 28 weeks’ gestation). The primary outcome is the incidence of successful intubation on the first attempt without physiological instability of the infant. Physiological instability is defined as an absolute decrease in peripheral oxygen saturation > 20% from pre-intubation baseline and/or bradycardia (< 100 beats per minute).

#### Research question

In neonates undergoing emergent or elective (with premedication) endotracheal intubation, does the use of nHF during laryngoscopy increase the likelihood of successful intubation on the first attempt without physiological instability, compared with no nHF?

### 8. Objectives

The primary objective of the SHINE trial is to investigate the efficacy of nHF in improving first attempt intubation success without physiological instability in neonates.

## Section 3: Study methods

### 9. Trial design

The SHINE trial is a multicentre, unblinded, randomised controlled trial investigating the efficacy of nHF to improve success and stability during neonatal endotracheal intubation. Intubations performed in the delivery room (DR) or neonatal intensive care unit (NICU) will be randomised, with a 1:1 ratio.

Infants will receive either:
Nasal HF during the endotracheal intubation attempt, orStandard care (no nHF during the endotracheal intubation attempt)

Full explanation of the trial design is included in the trial protocol [2].

#### Study protocol development and conduct

The SHINE trial was registered with the Australian and New Zealand Clinical Trials Registry (ACTRN126128001498280) on 6 September 2018. The trial was approved by the Human Research Ethics Committee of The Royal Women’s Hospital (Melbourne, Australia) on 8 November 2018 and by the Human Research Ethics Committee of Monash Health (Melbourne, Australia) on 1 March 2019.

The consent process involves written, prospective consent wherever possible from parents for inclusion of their infant in the study. However, in the event of an emergency intubation in the DR or within the first 24 h after admission to NICU, the study has approval to use a retrospective consent process at both study sites. The infant will be included in the study, then consent to continue (retrospective consent) will be sought from the parent or guardian as soon as possible after the procedure. This consent process was pursued due to the known safety and efficacy of nHF use in neonates and the lack of any anticipated risk compared with standard clinical practice.

An independent data and safety monitoring board (DSMB) is monitoring the study progress. The trial will be reported according to the Consolidated Standards of Reporting Trials (CONSORT) guidelines [3].

#### Outcomes

The primary outcome is the incidence of successful intubation at the first attempt without physiological instability.

Definitions and secondary outcomes are further outlined in Section 6 and in the trial protocol [2].

### 10. Randomisation

Each intubation episode is randomly allocated in a 1:1 ratio to either nHF or control, stratified by:
Centre (Royal Women’s Hospital or Monash Newborn),Postmenstrual age (≤ 28 weeks' gestation; > 28 weeks' gestation)Use of premedication for intubation.

The randomisation sequence uses random permuted blocks with varying block sizes. To enable rapid randomisation following the decision to intubate by the clinical team, the randomisation is performed at the cot-side using a smartphone or computer with online access to the Research Electronic Data Capture (REDCap) [4] randomisation tool. Randomisation is web-based, using a password-protected, secure sockets layer (SSL)-encrypted website. The randomisation sequence was developed by an independent statistician at the Murdoch Children’s Research Institute, Melbourne, Australia. The group allocations are unblinded, due to the nature of the intervention. Intubation episodes, rather than infants, are randomised. An infant who has previously had an intubation episode randomised within the study can have subsequent intubation episodes randomised if (1) the premedication randomisation stratum differs between the studied intubations or (2) there is at least 1 week between the studied intubations for intubations where premedications are used.

### 11. Sample size

The sample size of 246 intubation episodes is based on a previous study [5], which examined 206 neonatal intubations by junior medical staff. This study found a 29% successful intubation rate at the first attempt without peripheral oxygen desaturation > 20% or bradycardia < 100 beats per minute. With a power of 90% to detect an increase in the incidence of successful intubation without physiological instability from 30 to 50%, and two-sided alpha 0.05, at least 123 intubation episodes in each group (246 total) are required.

### 12. Framework

The SHINE trial is investigating the superiority of nHF, compared with standard ca

re (no nHF) for the primary outcome. Secondary outcomes will also be compared using a superiority framework.

### 13. Statistical interim analysis and stopping guidance

An external DSMB has been convened and is chaired by [name] (Liggins Institute, University of Auckland, New Zealand). The DSMB consists of two consultant neonatologists ([name] and [name]) and an independent statistician ([name]). The terms of reference of the DSMB were outlined in the SHINE trial DSMB charter (version 4, 25 June 2019) and ratified by the Trial Steering Committee and all members of the DSMB during the first DSMB meeting.

Safety analyses, including of pre-defined significant adverse events (SAEs), were planned and performed after recruitment of:
60 patients (~ 25% total)125 patients (~ 50% total) and180 patients (~ 75% total).

The defined SAEs were:
Incidence of pneumothorax within 72 h after randomisation, diagnosed either by transillumination of the chest and/or by chest X-rayIncidence of cardiac compressions and/or adrenaline administration within 1 h after the first intubation attemptDeath within 72 h after randomisation

After 125 patients were recruited (~ 50% total), an interim efficacy analysis was undertaken, comparing the two treatment groups (blinded) for the primary endpoint and its components:
Successful intubation on the first attempt without desaturation > 20% from baseline, or bradycardia < 100 bpmSuccessful intubation on the first attemptDesaturation > 20% from baselineBradycardia < 100 bpm

The information was presented by pseudo-labelled treatment arm (e.g. ‘A’ and ‘B’); the key to identify the treatment arms was able to be supplied by the independent statistician if requested by the DSMB.

As per the DSMB charter, the DSMB could recommend stopping the trial on the basis of *safety* using clinical judgement informed by statistical comparison of adverse event rates. Accumulating signals of harm did not necessarily require statistically significant differences to warrant an alert and recommendation from the DSMB. The DSMB were also able to consider recommending stopping the trial if there was a very strong statistically significant difference (*p <* 0.001) in the primary outcome between groups at the interim efficacy analysis. There was no planned adjustment of the significance level due to interim analysis.

At each time-point, the DSMB recommended continuation of the trial, with an unchanged protocol.

### 14. Timing of final analysis

Final analysis will be conducted after data entry is completed and the database cleaned and closed.

#### Data collection and management

Demographic data are collected on paper Case Report Forms, or by directly inputting data into the REDCap [4] database, by investigators at the recruiting hospitals. Each intubation episode is video recorded using a GoPro camera (GoPro, San Mateo, California), placed in a location that provides a clear overhead view of the intubation procedure, the infant’s face and the Masimo (Irvine, CA, USA) pulse oximeter. Each video recording is reviewed by an investigator to determine primary and secondary outcomes. The primary outcome is also recorded on the Case Report Form in real time, in case of video failure. Outcomes are then entered into an secure, password-protected, online electronic database (REDCap [4]) by an investigator at each hospital.

After data entry, records were reviewed for missing data. Requests for addition of missing data or clarification were resolved by an investigator at each site.

All data will be checked and cleaned by the trial statistician, A/[name], prior to analysis.

### 15. Timing of outcome assessments

The primary outcome is successful intubation on the first attempt, without physiological instability. The first intubation attempt is defined as the insertion and removal of laryngoscope beyond the baby’s lips.

The secondary outcomes are measured during the intubation episode (all intubation attempts for that infant) and up to 72 h after the intubation episode (for the pre-defined SAEs of pneumothorax, cardiac compressions and/or adrenaline administration, death).

## Section 4: Statistical principles

Overall principles

Data analysis will include all outcome data for all randomised intubation episodes. Analysis will start once all primary and secondary outcome are available, missing data has been sought, the database has been cleaned and locked, and the SAP has been submitted for publication.

### 17. Adjustment for multiplicity

All secondary outcomes will be reported as point estimates with unadjusted 95% confidence intervals only. There will be no adjustment for multiplicity.

### 18. Confidence intervals to be reported

For all outcomes, 95% confidence intervals will be presented.

### 19. Adherence and protocol deviations

### 20. Analysis population

The randomised population will comprise at least 246 intubation episodes, with infants randomised to either nHF or control. The analysis population will be created by removing the infants who met post-randomisation exclusion criteria from the randomised population, as outlined below.

On October 29, 2020, the Trial Steering Committee sought advice from the independent DSMB regarding post-randomisation exclusion criteria, with three deidentified randomisation episodes presented for discussion. These DSMB were blinded to trial data regarding the treatment arm and outcomes of the infants discussed.

Based on advice from the DSMB, the Trial Steering Committee reached consensus agreement regarding the following criteria for post-randomisation exclusions on 19 February 2021.
Randomised in error (patient was not intubated)Failure to meet inclusion criteriaMeeting exclusion criteria at the time of randomisation (e.g. bradycardia, abdominal wall defect)Parental withdrawal of consentParental consent declined in retrospective consent group

Therefore, the intention-to-treat (ITT) population will include all randomised infants and intubation episodes, regardless of exposure to the allocated treatment or adherence to the trial protocol, excluding the intubations which meet the post-randomisation exclusion criteria described above.

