#### Analyses- primary outcome

The primary analysis will be a modified intention to treat analysis, using the exclusion criteria outlined above. The primary outcome is a binary outcome, so as described above, the number and percentage of intubation attempts where there was successful intubation at the first attempt without physiological instability will be presented separately for the 2 treatment groups. Binary regression (a generalised linear multivariable model, with the primary outcome as the dependent variable, the group allocation as the predictor, and the stratification factors used during randomisation as covariates) will be used to estimate the difference between the treatment groups. The results will be reported as the difference in risk between the 2 treatment groups, with the 95% CI for the risk difference.

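### The SAP promises analysis of all randomised episodes but removes some afterwards under two different labels, and eligibility exclusions in this unblinded trial need neither a blind ruling nor a sensitivity analysis

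*SAP article*

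**What the plan says.** Four places in the SAP describe the population for the primary comparison.

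- Section 4, overall principles: "Data analysis will include all outcome data for all randomised intubation episodes".
- Section 20: "The analysis population will be created by removing the infants who met post-randomisation exclusion criteria from the randomised population". The remainder is named the intention-to-treat population and is kept "regardless of exposure to the allocated treatment or adherence to the trial protocol, excluding the intubations which meet the post-randomisation exclusion criteria described above".
- Section 26, Table 2: the block of primary results is headed as an intention-to-treat analysis.
- Section 27, primary outcome: "The primary analysis will be a modified intention to treat analysis, using the exclusion criteria outlined above".

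Section 20 lists five grounds. Three concern intubation and eligibility (the list items run together in the extracted text): "Randomised in error (patient was not intubated)Failure to meet inclusion criteriaMeeting exclusion criteria at the time of randomisation (e.g. bradycardia, abdominal wall defect". The other two are withdrawal of parental consent and refusal of retrospective consent.

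On process, section 20 says that the data and safety monitoring board (DSMB) gave advice after seeing three deidentified episodes, blinded to arm and outcome. Then, on 19 February 2021, "the Trial Steering Committee reached consensus agreement regarding the following criteria for post-randomisation exclusions". Section 9 states the design: "The SHINE trial is a multicentre, unblinded, randomised controlled trial". The SAP does not say who applies the criteria to an individual episode, or whether that person is kept from knowing arm and outcome.

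**The concern.** The statement in Section 4 cannot be true alongside section 20, and one analysis set carries two labels. A reader of the trial report could not tell from the SAP whether a result headed intention-to-treat includes every randomised episode.

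The larger issue is how the two eligibility grounds are applied. Allocation is known at the cot-side, and the outcome is known minutes later. If eligibility is settled after that, knowledge of either can affect the ruling, and exclusions may then differ between arms. Bradycardia is the sensitive case. Section 20 gives it as an example of an exclusion criterion met at randomisation, and section 26 makes a heart rate below 100 during the first attempt a failure on the primary outcome. A later judgement that the infant was already bradycardic would tend to remove episodes likely to count as failures.

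Ineligible infants who were intubated would normally have a primary outcome on video, with the case report form as backup (section 14). Leaving them out is therefore a choice that the data do not force, and nothing planned shows what that choice does to the estimate.

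**Working it through.** **Step 1. The texts side by side.**

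| Place | Who is analysed | Label |
|---|---|---|
| Section 4 | all randomised episodes | none |
| Section 20 | randomised minus five grounds | intention-to-treat |
| Section 26, Table 2 | not restated | intention-to-treat |
| Section 27, primary outcome | randomised minus the section 20 grounds | modified intention to treat |

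Section 4 conflicts with section 20 however many episodes are excluded. The labels in section 20 and Table 2 conflict with the one in section 27.

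**Step 2. Which grounds carry the risk.**

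- Not intubated: section 26 defines incidence over first intubation attempts, so an episode without an attempt has no primary outcome. The loss is unavoidable.
- Consent withdrawn or declined: also unavoidable.
- Inclusion criteria not met, or exclusion criteria met at randomisation: the episode may have been intubated and have a recorded outcome. These two grounds are where the risk lies.

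**Step 3. Does any planned analysis restore them?** The sensitivity analyses in section 27 address repeated randomisation of the same infant and imbalance in demographics. The per-protocol analysis concerns treatment received and moves further from all randomised episodes. None restores the ineligible episodes.

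**Step 4. The design figure.** Inputs from section 11: 30% versus 50%, two-sided alpha 0.05, power 90%, equal arms.

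n per arm = [1.96 × √(2 × 0.4 × 0.6) + 1.2816 × √(0.3 × 0.7 + 0.5 × 0.5)]² / 0.2² = 124.0

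The SAP states 123, and power at 123 is 89.8%. The design reproduces to within rounding, and the point does not depend on it.

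**Step 5. Illustrations of size.** The SAP gives no exclusion counts, so every count below is assumed. Each is a one-sided extreme in which all removed episodes are failures from a single arm. All figures are unadjusted.

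(a) At the design effect, the nearest whole counts are 62/123 and 37/123. Risk difference = 62/(123 − k) − 37/123.

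| k nasal high flow failures removed | Risk difference (points) | SE (points) |
|---|---|---|
| 0 | 50.4 − 30.1 = 20.3 | 6.1 |
| 4 | 52.1 − 30.1 = 22.0 | 6.2 |
| 8 | 53.9 − 30.1 = 23.8 | 6.2 |

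Four removals shift the estimate by 1.7 points, under a third of its standard error. The conclusion would not change.

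(b) Near the significance threshold, 51/123 versus 37/123 gives 11.4 points (95% CI −0.5 to 23.3; pooled z-test p = 0.063). Removing 4 nasal high flow failures gives 51/119 versus 37/123, or 12.8 points (0.7 to 24.8; p = 0.039).

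(c) With no true effect and common success rate p, removing k failures from one arm gives a spurious difference of 123p/(123 − k) − p. Type I error is from the normal approximation.

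| p | k | Spurious difference (points) | Two-sided type I error |
|---|---|---|---|
| 30% | 3 | 0.75 | 5.2% |
| 30% | 6 | 1.5 | 5.8% |
| 30% | 12 | 3.2 | 8.3% |
| 40% | 3 | 1.0 | 5.3% |
| 40% | 6 | 2.1 | 6.2% |
| 40% | 12 | 4.3 | 10.3% |

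A few exclusions do little, even if all are one-sided. About a dozen would matter.

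**The case against.** The case for the plan has real substance.

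- The eligibility grounds concern status fixed before allocation, and section 20 ties the exclusion criteria to the time of randomisation. Removing such episodes causes no bias if the ruling is blind, and an abdominal wall defect leaves little room for judgement. This stands. What is missing is a requirement for a blind ruling, and bradycardia is less clear-cut than a structural defect.
- The criteria followed blinded DSMB advice. They were agreed while primary data collection was still open (section 4 of the administrative information puts its completion after 1 April 2021), and the SAP version that carries them predates any data analysis. This protects the choice of criteria. It does not protect their application to each episode.
- Exclusions go into the CONSORT diagram (sections 21 and 24). That shows counts, but not the effect on the estimate.

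A reader might infer more than the SAP supports:

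- *That the Steering Committee or site staff sort episodes knowing the result.* The SAP does not say who classifies episodes, or what the Steering Committee knew. Its silence is the gap and is not evidence of unblinded decisions.
- *That dropping never-intubated episodes is itself a flaw.* They have no outcome under section 26, and section 10 places randomisation after the decision to intubate.
- *That exclusions leave the trial underpowered.* Removing 5% or 10% equally from 246 would give power of 88.2% or 86.4%. But those fractions are assumed, and section 20 expects at least 246 randomised episodes, so extra recruitment is not ruled out.
- *That the full randomised set must be primary.* Statisticians differ on this, and a modified set with a blind ruling and a sensitivity analysis is defensible.

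**Conclusion.** The point holds as a contradiction in the text together with an open risk of bias. The contradiction is certain: Section 4 is wrong as written, and one analysis set has two labels. The risk arises because allocation is unblinded, two eligibility grounds can be judged after arm and outcome are known, one example ground overlaps the primary outcome, and no analysis restores the episodes removed.

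Bias is not demonstrated. Its size depends on the number and imbalance of exclusions, which the SAP does not give. Under the assumed extreme of 4 one-sided removals the shift is 1.7 points against a design effect of 20. That would matter only for a result close to the significance threshold. With few or balanced exclusions the effect would be small. This should be fixed before database lock, but it does not invalidate the planned analysis.

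**What to change.** 1. Correct the statement in Section 4, and use modified intention to treat for the reduced set in section 20, Table 2 and section 27.
2. Require eligibility exclusions to be ruled on before database lock, from pre-randomisation data only, by someone without access to arm or outcome.
3. Add a named sensitivity analysis: the primary model fitted to all randomised episodes with usable consent and a first intubation attempt, including those later found ineligible.
4. Report exclusions by arm and reason, with never-intubated and no-consent episodes shown as unavoidable losses.

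The cost is SAP wording, a blinded check of a few records and one extra model run. The modified set can remain primary, so ineligible infants enter only the sensitivity analysis.

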#### Per-protocol analysis

We will undertake a per protocol analysis for the primary outcome if there are infants in the control group who received nHF or other apnoeic oxygenation during intubation or infants in the nHF group who never received the intervention. The following will not be deemed protocol violations: high flow prongs are placed and then dislodge or mechanical failure of machine.

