#### Primary outcome

The primary outcome is incidence of successful intubation at the first attempt without physiological instability, i.e. the proportion of first intubation attempts in which successful intubation without physiological instability occurs (Table 2).

**Table 2 Tab2:** Primary outcome and components

Outcome	Nasal HF group (*n =* XXX)	Control group (*n =* XXX)	Risk difference (95% CI)
Intention-to-treat analysis			
Successful first attempt intubation without physiological instability	XX (%)	XX (%)	
≤ 28 weeks’ GA	XX (%)	XX (%)	
> 28 weeks’ GA	XX (%)	XX (%)	
Premedication use	XX (%)	XX (%)	
No premedication use	XX (%)	XX (%)	
Inexperienced operator (< 20 previous intubations	XX (%)	XX (%)	
Experienced operator (≥ 20 previous intubations)	XX (%)	XX (%)	
Successful first attempt intubation	XX (%)	XX (%)	
Desaturation (SpO_2_ > 20% from baseline) during the first intubation attempt	XX (%)	XX (%)	
Bradycardia (HR < 100 bpm) during the first intubation attempt	XX (%)	XX (%)	

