#### Definitions

Intubation attempt: the insertion of the laryngoscope blade beyond the infant’s lips.Intubation duration: the time from the insertion of the laryngoscope blade beyond the infant’s lips until the removal of the laryngoscope blade from the infant’s mouth.Successful intubation: the completion of the intubation attempt with correct positioning of the endotracheal tube confirmed by detection of expired carbon dioxide on a colorimetric detector.Physiological instability: the incidence (any duration) of an absolute decrease in peripheral oxygen saturation (SpO_2_) > 20% from baseline (immediately prior to the intubation attempt), and/or bradycardia (heart rate < 100 beats per minute, bpm), during the first intubation attempt.

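### The per-protocol rule is not limited to the first attempt, where the primary outcome is decided, so exposure on a later attempt can determine who is analysed

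*SAP article*

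**What the plan says.** The per-protocol paragraph in section 20 of the SAP opens "We will undertake a per protocol analysis for the primary outcome if there are" and names two kinds of deviation: "infants in the control group who received nHF or other apnoeic oxygenation during intubation or infants in the nHF group who never received the intervention". It exempts two situations: "high flow prongs are placed and then dislodge or mechanical failure of machine". It gives no attempt number or time window for exposure. It implies, without stating, that deviating infants are left out.

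The outcome this analysis serves does have a window. Section 26 defines it as "the proportion of first intubation attempts in which successful intubation without physiological instability occurs", and physiological instability counts only "during the first intubation attempt".

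The SAP also recognises that an episode can contain more than one attempt. Section 15 says "The secondary outcomes are measured during the intubation episode (all intubation attempts for that infant", and the number of attempts is itself a secondary outcome in section 26.

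**The concern.** The outcome is settled at attempt 1, but the exposure that decides per-protocol membership is not confined to attempt 1. A second attempt normally takes place only because the first failed. Exposure on a later attempt is therefore a consequence of the outcome, and using it to choose the analysis set makes the selection depend on the outcome.

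The word *never* in the nHF limb matters most. An infant who received nHF on attempt 2 cannot be said never to have received it. The control limb is looser still, because *during intubation* is not defined.

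The per-protocol analysis is the only one in the SAP that addresses nHF as actually received, so readers will compare it with the main result. The trial is unblinded (section 9), so a change of support after a failed first attempt is possible. If the window is chosen only after outcomes are known, that choice is itself open to question.

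**Working it through.** **Inputs from the SAP (section 11).** 123 episodes per arm, 30% v 50%, 90% power, two-sided alpha 0.05. The usual two-proportion formula with pooled variance and no continuity correction gives 124 per arm (121 unpooled), and power at 123 is 89.8%. The planning figures therefore reproduce closely enough to use as a base.

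**Assumed inputs.** The SAP gives no deviation or crossover rates. All the rates below are assumptions, shown as ranges.

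**Who is removed if the rule is applied across all attempts**

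| Arm | First attempt | Later attempt | Status | Under a first-attempt rule |
|---|---|---|---|---|
| Control | no nHF or other apnoeic oxygenation; intubation fails | given it | removed (a primary-outcome failure) | kept |
| nHF | nHF missed; intubated | none | removed | removed |
| nHF | nHF missed; intubation fails | given nHF | kept as treated (a failure) | removed |
| nHF | nHF missed; intubation fails | not given nHF | removed | removed |

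The second row includes infants intubated at attempt 1 with instability. They are primary-outcome failures with no later attempt, and they are removed too.

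**Control arm.** Let *f* be the share failing intubation at attempt 1, and *q* the share of those given nHF or other apnoeic oxygenation only later. Removed = 123·f·q. Control rate = 0.30/(1 − f·q).
- f = 0.3, q = 0.05: removed 1.8; rate 0.30/0.985 = 30.5%; difference 50 − 30.5 = 19.5 points.
- f = 0.5, q = 0.10: removed 6.2; rate 0.30/0.95 = 31.6%; difference 18.4.
- f = 0.7, q = 0.20: removed 17.2; rate 0.30/0.86 = 34.9%; difference 15.1.

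Against 20 points under a first-attempt rule, the loss is 0.5 to 4.9 points.

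**nHF arm.** Let *m* be the share missing nHF at attempt 1 (30% of them primary-outcome successes, the rest of the arm at 50%), *f* their first-attempt intubation failure rate, and *s* the share of those failures given nHF later. A first-attempt rule gives 50.0%. The all-attempts reading gives 0.50(1 − m)/[(1 − m) + m·f·s].
- s = 0: 50.0%, no difference.
- m = 0.05, f = 0.7, s = 1: 0.475/0.985 = 48.2%.
- m = 0.10, f = 0.5, s = 0.5: 0.45/0.925 = 48.6%.
- m = 0.10, f = 0.7, s = 1: 0.45/0.97 = 46.4%, a loss of 3.6 points.

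Across these ranges, 30% to 100% of the nHF infants removed are primary-outcome successes.

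**One example in counts.** Take 37/123 v 62/123. Ten controls are exposed only on a later attempt. Ten nHF infants miss nHF at attempt 1: 3 succeed, and 7 fail and all get nHF later.
- All-attempts reading: 59/120 − 37/113 = 49.2% − 32.7% = 16.4 points.
- First-attempt rule: 59/113 − 37/123 = 52.2% − 30.1% = 22.1 points.
- All randomised: 62/123 − 37/123 = 20.3 points.

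With no true effect (37/123 in each arm) and the same deviations, the all-attempts reading gives 34/120 − 37/113 = −4.4 points. The first-attempt rule gives 34/113 − 37/123 = 0.0.

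**The case against.** The strongest reply is that the SAP does not say exposure counts at any point in the episode. A reader might infer that, but the paragraph uses neither the term episode nor any reference to later attempts. Section 9 words the allocated treatment in terms of a single attempt, section 26 measures intubation duration over one laryngoscope insertion, and the analysis is confined to a first-attempt outcome. This stands as far as it goes: *during intubation* could be read as the attempt. It does not rescue *never*, and elsewhere the SAP names the first attempt when it means it. The rule is therefore unlimited as worded, but it is not an explicit all-attempts rule.

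A reader might also infer that the rule strips successes from the nHF arm. That is too strong. It removes every nHF infant who never received nHF, failures included, and spares only failures treated later. Measured against modified intention-to-treat rather than a first-attempt rule, the nHF rate could move about 2 points either way.

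The bias also needs later-attempt crossover. The SAP does not say how common that is or whether it is allowed, and the protocol may cover it. The example above takes the upper case, in which every missed-nHF failure is treated later. Even so, its point estimate at the planned effect still favours nHF (16.4 points), so it does not support the inference that the analysis would show no benefit.

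Finally, this is a supportive analysis, run only if deviations occur. Section 27 makes modified intention-to-treat primary.

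**Conclusion.** The concern holds in limited form. The per-protocol rule is not tied to the attempt on which its outcome is decided. Applied as worded, it lets later exposure determine membership, and compared with a first-attempt rule it then biases the per-protocol estimate against nHF.

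On the assumed ranges, the control arm contributes about 0.5 to 5 points (2 to 17 of 123 controls removed). The nHF arm contributes from nothing up to about 4 points more (10% missing nHF at attempt 1, with all failures treated later). The bias is zero if no later-attempt crossover occurs. The direction relative to a first-attempt rule follows from the definitions, given that later attempts follow failed ones. The size rests wholly on the assumed rates. The primary result is not affected, so this is a correction worth making to a supportive analysis and not a threat to the trial's main conclusion.

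**What to change.** In the per-protocol paragraph of section 20, classify adherence by exposure during the first intubation attempt only:
- A control episode deviates if nHF or other apnoeic oxygenation was given during the first attempt.
- An nHF episode deviates if nHF was not applied for the first attempt.
- The existing exemptions for dislodged prongs and machine failure stay.
- Deviating episodes are excluded from the per-protocol analysis, stated explicitly.
- Exposure on later attempts does not affect per-protocol status and is tabulated separately by arm.

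This defines the analysis set only and does not bear on what support infants may receive on later attempts. The cost is a few lines of SAP wording, settled before analysis. First-attempt exposure should be readable from the video that section 14 says is made of each episode.
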